### 2.2 Participant recruitment

A total of 84 participants will be recruited through the acupuncture outpatient and inpatient systems, as well as advertisements of the First Affiliated Hospital of Tianjin University of Chinese Medicine. The recruitment will take the form of outpatient and inpatient acupuncture promotion, recruitment advertisements on official platforms, and legal social media. According to guidelines prepared by The American Psychiatric Association and the diagnostic criteria for mental disorders compiled by The Chinese Medical Association, patients who develop symptoms within 6 months after their first stroke will be recruited.

#### 2.2.1 Inclusion criteria

Participants who meet the following criteria will be included.

Diagnosed with stroke and meet the diagnostic criteria for “Mood disorder characterized by depression or accompanied by severe depressive episode caused by a stroke can also be characterized by mania or mixed characteristics (DSM- Ⅳ)” and “Depressive disorder due to another medical condition” in the Diagnostic and Statistical Manual of Mental Disorders, Fifth Edition (DSM-V) [22].Experience a first episode of stroke onset within 6 months.Age between 35 and 80 (inclusive).The HAMD score of 8 to 17 (inclusive).Clear consciousness, stable vital signs, cooperative physical examination.

#### 2.2.2 Exclusion criteria

Patients who have received antidepressant treatment within 2 weeks or are participating in other clinical trials for antidepressants.Patients who have consciousness disorder or obvious cognitive impairment function (Mini-mental State Examination score <17).Patients who have severe aphasia and cannot communicate.History of depression prior to this stroke event.Patients with severe liver and kidney dysfunction (alanine aminotransferase more than 3 times the upper limit of normal, and serum creatinine is more than 180 μmol/L).Pregnant and lactating women.Intolerance or refusal to receive acupuncture or electroacupuncture.

#### 2.2.3 Shedding criteria

Patients who have severe adverse effects will be removed from the experiment at the discretion of the researcher.Patients whose condition progresses during the experiment, influencing efficacy and safety decisions.Patients with low compliance (80% treatment compliance) or patients who received treatments not part of this trial.

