### 2.4 Blinding

Due to the characteristics and limitations of acupuncture operations, it is burdensome to blind acupuncture physicians, and we are unable to conduct a double-blind study design. Both the researchers and the operators are acquainted with the patient groups, and all patients will be treated in the acupuncture department by two licensed and experienced acupuncturists. Acupuncturists are not involved in the study design and are not allowed to communicate with patients about acupuncture operations and acupoint selection, and patients should also avoid communication with other patients. Because of the different acupuncture intervention methods, it is impossible to blind patients. To reduce the subjective influence, the evaluators are blinded to the distribution. In data management and statistical analysis, statisticians outside this study will be invited to participate. Admittedly, they will also be blinded to group information.

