#### 2.5.3 Sample size

In this study, HAMD-17 is used as the leading indicator for sample size calculation. Based on the results in the preliminary clinical study, i.e., observation of the Hamilton Depression Scale score reduction (ΔHAMD) results of 6.13 ± 1.96 Mean ± SD reduction in the test group and 4.57 ± 1.87 reduction in the control group, according to the sample size calculation formula.

$$\frac{2\;(Z_{\alpha /2}+Z_{\beta }{)}^{2}\times \sigma^{2}}{\delta^{2}}$$

α = 0.05, 1-β = 0.9, σ = 1.96, δ = (6.13–4.57) = 1.56

α is set to 0.05, the statistical power is set to 0.9, and a two-sided test is conducted. Based on the calculated dropout rate of 20%, each group will eventually require 42 patients; that is, a total of 84 participants will be randomly divided into two groups in a 1:1 ratio.

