### 2.8 Data collection and management

Before the start of the study, all researchers and acupuncturists will attend a three-day training course, including evaluation and collection, organized by the First Teaching Hospital of Tianjin University of Traditional Chinese Medicine. If participants can’t complete the study, these data will also be included in the statistics and kept. The case report form (CRF) will be used in this study to collect data. All personnel involved in data collection need to be confirmed and describe their work. Clinical researchers must fill in CRF accurately, timely, completely, and standardly according to the original information. The modification of CRF data must follow standard operating procedures, leaving traces of transformation. Once errors or discrepancies are found, researchers should be informed to ensure that all data records and reports are correct and complete. If necessary, the data management plan can be updated and revised in time according to the change in the research scheme, but corresponding procedures are needed to complete it. Data managers should thoroughly check the primary and secondary effectiveness indicators and key safety indicators specified in the system to ensure the correctness and integrity of these data. Any changes in the research plan will be notified to the ethics commission and the registration center promptly. This process will be carried out under the supervision of project supervision experts.

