### 2.9 Statistical analysis

Third-party statisticians who are not engaged in the allocation process or trial implementation will be invited to conduct statistical analysis and participate in the whole process, including trial design, implementation, and data analysis. Outcome measures at baseline and two-time points after the intervention will be analyzed to assess treatment effectiveness. Data will be analyzed using SPSS26.0 software according to the intention-to-treat principle of data analysis. Subgroup analysis will be performed if data for different clinical features are available. Chi-square tests will be used to assess sample characteristics and gender. Continuous variables will be summarized as mean ± standard deviation (SD). Continuous variables will be compared by the Student t-test or Wilcoxon rank sum test, and categorical variables will be reached by the Pearson chi-square test or Wilcoxon rank sum test reported by percentage. Data conforming to the normal distribution will be analyzed by one-way analysis of variance. The comparison of each group will be analyzed by T-test. A non-parametric rank sum test and the Mann-Whitney U test will be used to assess measurement data that does not have a normal distribution or homogeneous variance. A bilateral 5% significance level will be used, and the corresponding 95% confidence interval will be calculated as far as possible. P-value <0.05 would be set as the significance level, and the difference would be considered statistically significant.

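### The shedding criteria take randomised patients out on post-randomisation grounds, and the protocol does not reconcile this with its intention-to-treat analysis

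*Protocol article*

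**What the plan says.** Section 2.2.3 lists three shedding criteria that cover four grounds:

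- Severe adverse effects: "Patients who have severe adverse effects will be removed from the experiment at the discretion of the researcher".
- Progression: "Patients whose condition progresses during the experiment, influencing efficacy and safety decisions". No threshold and no decision-maker are given.
- Low compliance or other treatment: "Patients with low compliance (80% treatment compliance) or patients who received treatments not part of this trial". No decision-maker is given.

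Four other sections bear on what happens to these patients:

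- Section 2.4: "Both the researchers and the operators are acquainted with the patient groups", whereas "the evaluators are blinded to the distribution". Section 2.6 repeats that outcome assessment is blinded.
- Section 2.8: if participants cannot complete the study, "these data will also be included in the statistics and kept".
- Section 2.9: the data are analysed "according to the intention-to-treat principle of data analysis".
- Section 2.5.3: 42 patients per group, including a 20% allowance for dropout.

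Scale assessments are scheduled at baseline, week 2 and week 4 (sections 2.1 and 2.6, Table 1). No section says whether a shed patient still attends the later ones.

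**The concern.** Intention-to-treat means that patients are followed and compared as allocated, whatever treatment they go on to take. Shedding patients for poor compliance or outside treatment is a per-protocol rule. Shedding for progression or severe adverse effects selects on events that may be related to outcome and to treatment.

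The primary outcome needs a HAMD-17 score at week 4. If a shed patient is no longer assessed, that score does not exist, and the choice of analysis set cannot bring it back. The missing scores would then depend on how the patient was doing and on what treatment was received.

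The arms also differ in burden. Only the experimental group has the additional needles and the electro-stimulation (section 2.5.2), so unequal removal is plausible, though not established. For severe adverse effects the decision lies with a researcher, and section 2.4 says that researchers know the allocation. Blinded rating does not protect against selection that happens before the rating.

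**Working it through.** **1. Do the sections fit together?**

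- Section 2.2.3 speaks of removal from the trial itself. Section 2.7, by contrast, speaks of stopping treatment. The natural reading of 2.2.3 is that the patient leaves.
- Section 2.8 protects data already collected. A patient shed before week 2 contributes a baseline only. One shed between weeks 2 and 4 contributes baseline and week 2. Neither has a week-4 value unless assessment continues.
- Section 2.9 names t-tests, analysis of variance and rank tests. A comparison at week 4 by any of these needs a week-4 value for each patient.

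So 2.8 and 2.9 intend to include everyone, while 2.2.3, followed as written, can prevent the data needed for this from being collected.

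**2. The plan's own sample size (section 2.5.3)**

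Inputs: two-sided α = 0.05, power 0.90, σ = 1.96, δ = 6.13 − 4.57 = 1.56, dropout 20%.

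- n = 2(1.960 + 1.282)² × 1.96² / 1.56² = 33.17 per group.
- 33.17 / (1 − 0.20) = 41.5, rounded up to 42. The stated figure reproduces. Rounding to 34 first gives 34 / 0.8 = 42.5, or 43, a trivial difference.
- Power on these inputs is 95.4% with 42 per group analysed and 90.7% with 34.

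The allowance therefore covers the loss of numbers. It does nothing about bias.

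**3. Worst-case illustration of bias**

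These assumptions are not in the protocol: no true difference, normally distributed reductions with SD 1.96, 42 randomised per arm, the patients with the smallest reductions removed, and only the remainder compared by t-test (20,000 simulated trials per row). With whole patients, 5%, 10% and 20% of 42 are 2, 4 and 8.

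| Removed, control | Removed, experimental | Spurious difference (points) | Two-sided rejection rate |
|---|---|---|---|
| 0% | 0% | 0.01 (simulation error) | 4.9% |
| 10% | 10% | 0.00 | 8.3% |
| 20% | 20% | 0.00 | 10.1% |
| 10% | 20% | 0.29 | 15.6% |
| 5% | 20% | 0.45 | 23.0% |
| 0% | 20% | 0.64 | 34.7% |

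Analytic check: truncating the worst 20% of a normal distribution shifts its mean by 0.35 SD, and the worst 10% by 0.195 SD. The difference is (0.35 − 0.195) × 1.96 = 0.30 points, which agrees with 0.29.

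Against the planned effect, 0.29 / 1.56 = 19% and 0.45 / 1.56 = 29%. The sign depends on which arm loses more: interchanging the arms reverses it. Equal removal leaves the difference unbiased, but rejection rises because truncation shrinks the SD.

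**4. The compliance figure**

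Six sessions a week for four weeks is 24 sessions, and 80% of 24 is 19.2. No whole number of sessions falls exactly on the limit, so for sessions it makes no difference whether the limit itself counts as low.

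**The case against.** The strongest reply is that sections 2.8 and 2.9 already state the right intention, and that a full protocol or analysis plan, not shown, may settle missing data and follow-up after stopping treatment. Much of this stands, and it rules out several stronger readings.

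- A reader might infer that intention-to-treat is defeated or cannot be carried out. No section says that shed patients leave the analysis set, and 2.8 points the other way. A patient shed after week 2 would also have a post-baseline score.
- A reader might infer that unblinded researchers decide on all four grounds. Discretion is written only for severe adverse effects, and the outcome evaluators are blinded.
- A reader might infer that the 80% rule has no direction. The word low supplies it. Only a formal inequality is missing, which is editorial.
- A reader might take progression to mean poor antidepressant response. The criterion does not name the condition. These are recent stroke patients, so neurological deterioration is as possible a reading.
- A reader might take the 20% dropout figure as the expected amount of shedding. It is a general planning allowance and says nothing about how many patients these criteria would remove.

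What the reply does not remove is the conflict itself. Section 2.2.3 is a stated rule, not a detail left to another document, and keeping data already collected is not the same as continuing to collect them.

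**Conclusion.** The point holds as a conflict to be reconciled. Section 2.2.3 sheds randomised patients on post-randomisation grounds, section 2.9 promises intention-to-treat, and section 2.8 does not close the gap because it is silent on assessment after shedding.

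The harm is conditional. It needs removal to end assessment, and bias in the difference also needs removals that differ by arm in number or in kind. The size cannot be estimated from the protocol. About 0.29 points with 16% type I error (20% versus 10% removed), and about 0.45 points with 23% (20% versus 5%), are worst-case values under assumed rates and should not be read as forecasts. Severe adverse effects, missed sessions and outside treatment need not follow HAMD-17 response so closely.

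It should be settled before outcome data accrue, because week-4 scores that were not collected cannot be recovered.

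**What to change.** Reconcile section 2.2.3 with sections 2.8 and 2.9:

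1. State that shedding means stopping trial treatment, not leaving the study. Record the ground and the date. Leave the clinical grounds for stopping treatment unchanged.
2. Keep the scheduled week-2 and week-4 scale assessments (HAMD-17, SDS, NIHSS, MBI) for every randomised patient unless consent is withdrawn.
3. State that the primary result includes all randomised patients as allocated.
4. Use compliance (written as below 80%, if that is what is meant) and non-trial treatment only to define a per-protocol sensitivity set.

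The cost is a change of wording, plus at most two already scheduled scale visits for each patient who stops treatment.

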#### 2.2.4 Termination criteria

Severe safety issues occurred during the trial.The situation where the study does not have any clinical value, i.e., The effect of acupuncture or electroacupuncture is much lower than that of modern medicine on the market.

### 2.3 Randomization

The randomization sequence will be generated by an independent statistician with the PROCPLAN procedure of the SAS9.3 statistical analysis system, which will not be involved in other trial procedures. To ensure allocation concealment, the generated random allocation sequence is placed in a sequentially coded, sealed opaque envelope, which will be opened in series, and the subjects will be assigned to either the observation or control group after the researcher determines the subject’s eligibility. To minimize bias, the allocation sequence cards in the envelope will be force-sensitive recording paper, and the researcher’s names of eligible subjects will be inscribed on the surface of the envelope before opening.

### 2.4 Blinding

Due to the characteristics and limitations of acupuncture operations, it is burdensome to blind acupuncture physicians, and we are unable to conduct a double-blind study design. Both the researchers and the operators are acquainted with the patient groups, and all patients will be treated in the acupuncture department by two licensed and experienced acupuncturists. Acupuncturists are not involved in the study design and are not allowed to communicate with patients about acupuncture operations and acupoint selection, and patients should also avoid communication with other patients. Because of the different acupuncture intervention methods, it is impossible to blind patients. To reduce the subjective influence, the evaluators are blinded to the distribution. In data management and statistical analysis, statisticians outside this study will be invited to participate. Admittedly, they will also be blinded to group information.

### 2.5 Interventions and comparison

All patients will receive primary rehabilitation treatment during the 4-week trial. Patients with stroke and its high-risk underlying conditions (e.g., hypertension, diabetes, coronary artery disease) will be treated with secondary care and appropriate essential medication according to China’s Guidelines for the Prevention and Treatment of Cerebrovascular Diseases. The physicians involved in the trial are highly qualified physicians with master’s degrees in acupuncture and moxibustion from the First Teaching Hospital of Tianjin University of Traditional Chinese Medicine, who have undergone uniform and standardized training in the operation protocol and are highly experienced. For four weeks, patients will receive (electro)acupuncture in the supine or semi-supine posture once a day, six times a week. The specific operations are as follows.

#### 2.5.1 Control group

Patients in the control group will receive conventional rehabilitation treatment with medication and acupuncture for 4 weeks.

Acupuncture treatment based on XNKQ Acupuncture for stroke dysfunction, acupoint locations are as described in **Table 2**. Acupoints include Shuigou (DU26), bilateral Neiguan (PC6), affected side Sanyinjiao (SP6), affected side Jiquan (HT1), affected side Chize (Lu5), affected side Weizhong (BL40), affected side Hegu (LI4), affected side Zusanli (ST36). The patient is placed in a supine position. After skin disinfection, the acupuncturist holds a disposable acupuncture needle (0.25mm×40mm Hwato brand, Suzhou Medical Supplies Factory Co., Ltd., Suzhou, China) for acupuncture operation. It should be noted that XNKQ Acupuncture uses a specific operation method, which is explained in Table 2. The acupuncture method is used to “De Qi” before the acupuncture is performed. Then all needles would be removed after being retained for 30 minutes. All patients will receive treatment six times each week for four weeks.Oral escitalopram tablets 10mg Qd for 4 weeks.

**Table 2 pone.0303162.t002:** Specific acupuncture methods and locations of acupoints.

Acupoints	Location	Insert angle	Insert depth
Baihui* (DU20)	On the head, 5 cun directly above the midpoint of the anterior hairline	15°	3 to 5 mm
Yintang* (EX-HN3)	On the head, at the intersection of the line between the two brows and the front midline	45°	10 to 15 mm
Fengfu* (DU16)	On the neck, 1 cun straight above the middle of the posterior hairline, the external occipital protuberance goes straight down, and the depression between the trapezius muscles on both sides	45°	15 to 20 mm
Shen* (CO10)	Located in the auriculae boat, on the ear wheel, below the foot fork, on the ear wheel foot below the rear, the 10^th^ area of the concha	90°	2 to 3 mm
Xin* (CO15)	Located in the depression in the middle of the concha cavity, that is, the 15th area of the concha	90°	2 to 3 mm
Shuigou**(DU26)	On the face, at the intersection of the upper 1/3 and middle 1/3 of the human midsulcus. In the orbicularis muscle (Sparrow-pecking acupuncture techniques until the eyeballs are wet with tears)	45°	5 to 10 mm
Neiguan** (PC6)	On the palm side of the forearm, between the palmaris longus tendon and the flexor carpi radialis tendon	90°	10 to 15 mm
Sanyinjiao** (SP6)	On the medial side of the shank,3 cun above the medial malleolus, by the posterior of the tibia (Make the patient’s limbs twitch three times)	45°	20 to 25 mm
Jiquan** (HT1)	At the axilla apex, where the axillary artery beats. (Make the patient’s limbs twitch three times)	45°	20 to 25 mm
Chize** (Lu5)	In the transverse stripes of elbow, the radial depression of biceps brachii tendon (Make the patient’s limbs twitch three times)	45°	20 to 25 mm
Weizhong** (BL40)	Located in the posterior region of the knee, at the midpoint of the popliteal transverse stripes. (Make the patient’s limbs twitch three times)	45°	20 to 25 mm
Hegu** (LI4)	On the dorsum of the hand, between the first and second metacarpal bones, approximately in the middle of the second metacarpal bone on the radial side	90°	20 to 25 mm
Zusanli** (ST36)	Lateral leg, 1 cun away from the anterior tibial crest.	45°	20 to 25 mm

* = Acupoints in Antidepressant acupuncture group. ** = Acupoints in Control group

#### 2.5.2 Antidepressant acupuncture group

The patients will be placed in a semi-supine position, i.e., the bed rocker is elevated to 45°, and after skin disinfection, the treatment proceeds as follows.

The exact XNKQ acupuncture as in the control group is given, and the same acupuncture method is used to “De Qi” before the antidepressant acupuncture is performed [23]. Lifting-thrusting and twirling-rotating manipulations are acupuncture procedures used to make patients feel "De Qi," such as soreness, numbness, and swelling.Antidepressant acupuncture is given. The acupoint selections and ear-treating areas are Baihui (DU20), Yintang (EX-HN3), Fengfu (DU16), and auricular concha (corresponding to the auricular point Xin (CO15) and auricular point Shen (CO10)). The specific acupoint locations and operation diagram are shown in **Table 2** and Fig 2. The specific operations are as follows. The Baihui (DU20) point is inserted to a depth of 3 to 5 mm at an angle of 15°. The Yintang (EX-HN3) point is inserted to a depth of 10 to 15 mm at an angle of 45° (Needle tip towards the root of the nose). The Fengfu (DU16) point is inserted to a depth of 15 to 20 mm at an angle of 45° (Needle tip towards the Laryngeal node area). The auricular concha is equivalent to the position of the auricular point Xin (CO15) and auricular point Shen (CO10) of the auricular acupoint, with a depth of 2 to 3 mm and an angle of 90°. The two electrode clamps of the electroacupuncture instrument are then clamped to the shanks of the two acupuncture needles. Baihui (DU20) and Yintang (EX-HN3), connected to a group of electro-acupuncture, auricular acupoint Xin (CO15) and acupoint Shen (CO10) connected to another group of electro-acupuncture (Hwato SDZ-IIB type electro-acupuncture instrument, Suzhou, China). The researcher set the frequency at 2/15Hz, the intensity at 2mA, and the time at 30min, and alternately acupuncture/electro-acupuncture at bilateral auricular acupoints. All patients will be treated once a day, 6 sessions per week for 4 weeks.

**Fig 2 pone.0303162.g002:**
[figure not shown]
Auricular concha acupoints Shen(CO10) Xin(CO15) acupoints Bai-Hui(Du20) Yin-Tang(EX-HN3) Feng-Fu(DU16).

